### 2.3. Protocols

The percentage of adherence to the physical exercise programs, for each program, will be calculated considering the total attended sessions: (S × 100)/T, where “S” indicates the number of sessions that have been attended by the participant during the study and “T” indicates the total number (56) of physical exercise sessions. The participants’ attendance will be recorded in a database. If a participant has two consecutive absences, they will be contacted and given motivational reinforcement to incentivize them to resume their physical exercise sessions.

During the study period, all adverse effects or health problems attributed to the physical exercise sessions or evaluation tests will be reported. Parameters such as muscle pain, excessive fatigue and general pain will also be reported and inserted in a database. Exercise technicians and researchers will be responsible for data collection as well as for gathering and communicating all relevant data.

Three physical exercise programs will be conducted for a time period of 28 weeks, two times per week (non-consecutive days) and have the following common characteristics: all sessions will have a duration of 45 min, taking into account previous studies [10] that suggest sessions of this duration seem to be sufficient to provide changes in several parameters in the elderly population; they will be aquatic-based (the water level will be between 0.80 and 1.20 m with a temperature of approximately 32 °C); and they will be conducted to the rhythm of music (bpm) that can be adjusted to achieve the target HR. Sessions are divided into three parts: the initial part, main part and final part, with common exercises in the initial and final part of the three programs. The initial part or warm-up has a duration of 10 min and the purpose is to assist participants to adapt to the water environment, more specifically, for participants’ to acclimatize and prepare for muscular and metabolic stimulation. Simple aquatic-based exercises will be conducted, e.g., displacement and isolated movements. The exercises increase in complexity and intensity during this initial phase. The final part has a duration of 5 min. This part will be divided into two phases: return to calm (relaxation) where relaxing exercises are conducted with the purpose of returning the participants’ heart rate (HR) value to a resting level. The second phase is composed of stretching routines that stretch the most exercised muscle groups stimulated in the main part of the session and reduce the level of lactic acid and the occurrence of post-exercise pain. The main part is different in the three physical exercise programs and their characteristics are described in Table 1. All physical exercise programs will be planned and implemented according to the recommendations of the American College of Sports Medicine [19] and conducted by specialized physical exercise technicians (with a degree in sports science) with specialization in hydro-gymnastics (instructor course—level 1).

HR monitors (Polar V800) will be used on the participants during all sessions of the different physical exercise program. The intensity of each exercise program will be monitored using the data provided by the Polar V800 and adjusted accordingly. As a precaution and safety measure, the intensity will be indirectly calculated using the following equation [20]:(1)Target HR=((Maximum HR−Resting HR) % intensity)+Resting HR

*Maximum HR* is calculated with the following equation for senior populations [21]:(2)Maximum HR=207−(0.7×age)

The control group consists of non-institutionalized individual participants who have not partaken in any physical exercise during the preceding year. These participants will be encouraged to conduct their daily activities as usual, except for the data collection (M1 and M2) organized by the researchers.

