## Abstract

Cardiometabolic diseases are one of the primary causes of mortality and morbidity worldwide and sedentary lifestyles are contributing factors to these pathologies. Physical exercise has been recognized as an important tool in the prevention and treatment of these diseases. However, there are still some doubts about the efficacy of certain type of physical exercise programs for older participants. The main goal of this study is to assess the impact of different aquatic-based physical exercise programs on risk markers of cardiometabolic diseases in older people. The study group will consist of non-institutionalized individuals, within the age group of 65 or older. The sample will be randomly divided into four groups, three experimental groups (EG) and one control group (CG). Participants from the EGs will be exposed to three physical aquatic-based exercise programs for a period of 28 weeks (continuous aerobic, interval aerobic and combined). The evaluated parameters include anthropometry, physical functions, mental health, cognitive function, carotid arteries intima-media thickness, heart rate variability and biochemical markers. The results will allow an interpretation of the impact of different aquatic-based physical exercise programs on cardiometabolic diseases markers and can also be used as a tool for professionals to prescribe adequate and more efficient physical exercise programs.

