### 2.2. Participants

The participants were recruited in the central area of Portugal, more specifically in the region of Sertã. The sample was recruited by the non-probabilistic method for convenience. One hundred and fifty individuals from the community were personally invited, but only 102 agreed to participate in the study (mean age of 72.32 ± 5.2 and BMI 29.47 ± 4.85). Participants will be selected according to the following inclusion criteria: individual of both genders; age equal to or above 65 years of age; non-institutionalized individuals; they give permission to be part of the study and if the participant presents with a clinical condition or comorbidity, it must be stable and enable participation in aquatic-based exercises classes as approved by local medical staff. The exclusion criteria are: individuals less than 65 years of age; individuals with medical diagnosed pathologies that jeopardize their health while preforming aquatic based exercises, participants that attend less than 50% of all the sessions and participants who cannot complete all of the proposed tests.

The participants will be distributed randomly into different exercise groups based on their registration for one of the schedules offered for the hydro-gymnastics sessions. There will be three distinct schedules (9.00, 9.50 and 10.40), with the constraint being that the participants must attend the same schedule for the whole year. The 9.00 session includes the continuous aerobic program, the 9.50 session includes the interval aerobic program, and the 10.40 session includes the combined exercise program. This information will not be provided to participants before they register for the sessions so it will not be possible to establish any association between the schedule and the different exercises programs. Such information will be communicated later in the study. The control group will be randomly recruited from the community and will include those individuals that have not been involved in any kind of physical exercise during the last year.

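### Health problems are recorded only if attributed to sessions or tests, so event rates in exercisers and controls cannot be compared like for like

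*Protocol article*

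**What the plan says.** Section 2.3 (Protocols) contains the article's rules on harms. The main rule is that "all adverse effects or health problems attributed to the physical exercise sessions or evaluation tests will be reported", and it applies throughout the study period. The next sentence adds a short list of symptoms: "Parameters such as muscle pain, excessive fatigue and general pain will also be reported and inserted in a database". That sentence has no attribution condition and no restriction to the exercise groups, but it gives no timing or method of collection. On responsibility, the section says: "Exercise technicians and researchers will be responsible for data collection as well as for gathering and communicating all relevant data".

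The same section describes the contact each group has with the study. For exercisers, the T in the adherence formula "indicates the total number (56) of physical exercise sessions", and anyone who misses two sessions in a row is contacted. Controls are "encouraged to conduct their daily activities as usual, except for the data collection (M1 and M2) organized by the researchers".

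Section 2.2 (Participants) lists among the exclusions "participants that attend less than 50% of all the sessions and participants who cannot complete all of the proposed tests".

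**The concern.** The usual practice is to record every adverse event in every group and to note the judged relation to the intervention in a separate field. Here the relation is the condition for recording. This has two consequences.

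First, an event can be linked to a session only in someone who attends sessions, so the rule works differently in the exercise and control groups. More events recorded in exercisers could be produced by the rule alone. A real benefit outside the pool, such as fewer falls at home, would be invisible.

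Second, events caused by a programme but not recognised as such at the time are missed. Only an unfiltered count, set against a control group, could reveal them.

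Participants are aged 65 or over, with a mean age of 72.32 among those who agreed to take part, and stable comorbidity is allowed. Background illness is therefore to be expected. The abstract offers the results as a tool for professionals who prescribe exercise, and such readers will want to know how health events compared with no programme.

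**Working it through.** The article gives no harms figure to reproduce, so the check sets its statements side by side and adds simple arithmetic.

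**1. What is recorded, by group (section 2.3)**

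| Type of event | Exercise groups | Control group |
|---|---|---|
| Attributed to a session | Recorded | Cannot occur |
| Attributed to an evaluation test | Recorded | Recorded |
| Listed pain and fatigue symptoms | Recorded, schedule not stated | Not excluded, schedule not stated |
| Other health problem, not attributed | Not required | Not required |

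The first row makes the groups unlike. The last row loses events in all four groups.

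**2. Occasions to which an event can be attributed**

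- Exerciser: 2 sessions × 28 weeks = 56 sessions, which agrees with the article's total. Adding M1 and M2 gives 56 + 2 = 58 at full attendance.
- Control: 2 (M1 and M2).
- Contact after repeated absence is described in connection with session attendance, so it also exists only for exercisers.

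**3. Effect of the rule when true rates are equal**

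Let p be the true proportion with a health event over 28 weeks, the same in both groups, and let a be the share of those people in the exercise groups whose event is attributed to a session. Assume that test-attributed events are equally common in both groups and cancel.

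- Recorded in exercisers: a × p
- Recorded in controls: 0
- True difference: 0; recorded difference: a × p, which is above 0 whenever a is above 0
- Unrecorded: (1 − a) × p in exercisers and p in controls

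**4. Illustrative size**

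The article gives neither group sizes nor an event rate. Splitting the 102 who agreed to take part evenly over four groups gives 102 / 4 = 25.5, say 25 controls. Assume p between 10% and 40%.

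- 25 × 0.10 = 2.5 people
- 25 × 0.40 = 10 people

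With the planned total of 76 instead, 76 / 4 = 19 controls, giving 19 × 0.10 = 1.9 to 19 × 0.40 = 7.6 people. In each case, events not attributed to a test fall outside the rule.

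**5. What complete recording could achieve**

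Power of a two-sided Fisher exact test at 0.05, with the assumed 25 per group:

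| True proportions (control vs exercise) | 25 vs 25 | 25 controls vs 75 pooled exercisers |
|---|---|---|
| 10% vs 20% | 0.09 | 0.14 |
| 10% vs 30% | 0.30 | 0.49 |
| 40% vs 60% | 0.24 | 0.35 |

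Zero events in 25 people leaves a one-sided 95% upper bound of 1 − 0.05^(1/25) = 0.113, about 11%. Like-for-like recording removes the bias, but it cannot turn the comparison into a test of safety.

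**The case against.** The strongest reply is that the stated aim is the effect on risk markers. No harms objective or harms comparison is declared, and groups of this size could not show safety even with perfect recording (step 5). An article also condenses a fuller protocol, where event forms and follow-up of controls commonly sit. Much of this stands. It rules out any claim that the trial fails an objective, and it limits the remedy to descriptive reporting. It does not remove the point, because the attribution condition is a rule the article states, not a detail it leaves out.

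Stronger readings are tempting, but the text does not support them:

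- **Controls yield no harms data.** Test-attributed events can arise in controls, and the symptom sentence does not exclude them. The EQ-5D, which covers pain or discomfort and mobility (section 2.4.6), is among the measures for both assessments. It is not an event record, but it is comparable information.
- **The programmes' harms cannot be judged.** The three programmes share session frequency, length and setting, so attributed events can be described for each and compared among them.
- **Class staff decide what counts.** Technicians and researchers collect the data. The article does not say who judges attribution.
- **Harms in low attenders are discarded.** Someone who stops for health reasons before attending 28 of the 56 sessions meets the exclusion in section 2.2. Nothing says that their adverse-event records are dropped, and the contact after absences could bring a health reason to light.

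**Conclusion.** The point holds for the comparison of exercise with control. Following section 2.3 as written, health problems not attributed to a session or test need not be recorded in any group, and session-attributed events can arise only in exercisers. Event rates in the two kinds of group would differ by recording rule, with up to 58 occasions for attribution against 2.

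The conclusion rests on the article's wording and on M1 and M2 being the only control contact it describes. The 2.5 to 10 affected controls rest on an assumed event rate and an assumed even split, and the conclusion does not depend on them. A fuller protocol may describe more follow-up of controls, but it would have to depart from the published rule to cure the problem. This is a modest, inexpensive improvement to the plan, and it does not affect the risk-marker results.

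**What to change.** Change the rule in section 2.3 so that all adverse events and health problems, together with the listed symptoms, are recorded whether or not they are attributed to the study.

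- Use one identical short recall form at M2 in all four groups, covering the period since M1. Complete it by telephone for those who stopped attending.
- Record judged attribution in a separate field.
- Tabulate descriptively by group, including participants below 50% attendance and those who did not complete all tests.
- Report events learned at sessions or through absence contacts in a separate table for the three programmes. These routes exist only for exercisers, so using them in the comparison with control would bring back unequal recording.

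The cost is a short form, a few telephone calls and one extra table. Recall over 28 weeks will miss minor events, but by the same method in every group. The comparison stays descriptive because the groups are small.

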## Figures and Tables

**Table 1 ijerph-17-08678-t001:** Characteristics of the three physical exercise programs applied for 28 weeks (continuous aerobic, interval aerobic and combined).

Program	Description	Intensity (Week 1–13)	Intensity (Week 14–28)	Exercises
Continuous Aerobic	30 min exercise aerobic (moderate intensity)	60–65% maximum HR	65–70% maximum HR	Basic hydro-gymnastics exercise, with some variations: running, bounce, kicking, pendulum jumping, skiing, twister and horse.
Interval Aerobic	10 min exercise aerobic (moderate intensity)	60–65% maximum HR	65–70% maximum HR	Basic hydro-gymnastics exercise, with some variations: running, bounce, kicking, pendulum jumping, skiing, twister and horse.
	5 min exercise aerobic (high intensity)	70–75% maximum HR	75–80% maximum HR	
	10 min exercise aerobic (moderate intensity)	60–65% maximum HR	65–70% maximum HR	
	5 min exercise aerobic (high intensity)	70–75% maximum HR	75–80% maximum HR	
Combined	15 min exercise aerobic (moderate intensity)	60–65% maximum HR	65–70% maximum HR	Basic hydro-gymnastics exercise, with some variations: running, bounce, kicking, pendulum jumping, skiing, twister and horse.
	15 min muscular strengthening exercises	2 steps 12 repetitions	3 steps 16 repetitions	Exercises with auxiliary equipment (dumbbells, pool noodles, etc.): elbow extension/flexion; shoulder extension/flexion; shoulder abduction/adduction; hip abduction/adduction; hip flexion/extension; knee flexion/extension; dorsal and plantar flexion of the ankle.

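### Table 1 states the aerobic intensity as a percentage of maximum heart rate, but the protocol's only target formula applies the percentage to heart-rate reserve, so the two give different exercise doses

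*Protocol article*

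**What the plan says.** Section 2.3 of the protocol article states that "the intensity will be indirectly calculated using the following equation" and then gives equation 1: "Target HR=((Maximum HR−Resting HR) % intensity)+Resting HR". The percentage multiplies the difference between maximum and resting heart rate, and resting heart rate is added back. No other target formula appears in the article. Equation 2 in the same section predicts maximum heart rate from age, as 207 minus 0.7 times age.

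Table 1 lists the programmes in columns headed by intensity and period, the first being "Intensity (Week 1–13". Every aerobic band there, in all three programmes, is expressed as a percentage of maximum heart rate. The bands run from "60–65% maximum HR" for moderate work in the first period to "75–80% maximum HR" for high-intensity work in the second.

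The target is used in practice. Section 2.3 says of the sessions that "they will be conducted to the rhythm of music (bpm) that can be adjusted to achieve the target HR", and that heart-rate monitors are worn in all sessions and used to correct the intensity.

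**The concern.** A percentage of maximum heart rate and the same percentage of heart-rate reserve are different prescriptions. Table 1 supplies the percentages, equation 1 is the only rule for turning a percentage into a target, and the label on the percentages does not match the rule. Someone working from Table 1 and someone working from equation 1 would set different heart-rate targets for the same participant.

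Exercise intensity is the dose of the intervention and part of what separates the three programmes. The conflict therefore affects how hard people aged 65 or older are asked to work, the size of the moderate-to-high step that defines the interval programme, and what a later reader would reproduce from the published table. The heart-rate recordings cannot show whether participants met the target while the target has two values.

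**Working it through.** **Inputs**

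- Equation 1 (Section 2.3): target = p × (max − rest) + rest.
- Table 1 label taken literally: target = p × max.
- Equation 2 (Section 2.3): "Maximum HR=207−(0.7×age", closing bracket to follow.
- Values of p from the Table 1 bands: 0.60 to 0.80.
- Age: 72, rounded from "mean age of 72.32 ± 5.2" in Section 2.2.
- Resting heart rate: not given in the article. Assumed 70 bpm, with a range of 50–90.

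The protocol prints no target in bpm, so there is no stated figure to reproduce.

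**Gap between the two definitions**

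[p × (max − rest) + rest] − p × max = rest × (1 − p)

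Maximum heart rate cancels, so the gap in bpm does not depend on age. It is positive for any resting heart rate.

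**Targets at age 72**

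Maximum heart rate = 207 − 0.7 × 72 = 156.6 bpm. With rest 70, equation 1 becomes 86.6 × p + 70.

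| p | Table 1 label (bpm) | Equation 1, rest 70 (bpm) | Gap, rest 70 (rest 50–90) |
|---|---|---|---|
| 60% | 94.0 | 122.0 | 28 (20–36) |
| 65% | 101.8 | 126.3 | 24.5 (17.5–31.5) |
| 70% | 109.6 | 130.6 | 21 (15–27) |
| 75% | 117.5 | 135.0 | 17.5 (12.5–22.5) |
| 80% | 125.3 | 139.3 | 14 (10–18) |

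A five-point band is 0.05 × 156.6 = 7.8 bpm wide on the Table 1 scale. The smallest gap in the table, 10 bpm (80%, rest 50), already exceeds that.

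**Equation 1 targets as a percentage of maximum heart rate**

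This is p + (1 − p) × rest/max.

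| p | rest 50 | rest 70 | rest 90 |
|---|---|---|---|
| 60% | 72.8 | 77.9 | 83.0 |
| 65% | 76.2 | 80.6 | 85.1 |
| 70% | 79.6 | 83.4 | 87.2 |
| 75% | 83.0 | 86.2 | 89.4 |
| 80% | 86.4 | 88.9 | 91.5 |

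With rest 70, the lowest moderate target under equation 1 is 77.9% of maximum, inside the 75–80% band that Table 1 calls high intensity in weeks 14–28. Age matters little here: with rest 70, the 60–65% band becomes 77.3–80.2% at age 65 (maximum 161.5) and 78.5–81.2% at age 80 (maximum 151.0).

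**Moderate-to-high step in the interval programme (10 points)**

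- Table 1 label: 0.10 × 156.6 = 15.7 bpm.
- Equation 1: 0.10 × (156.6 − rest) = 10.7, 8.7 and 6.7 bpm for rest 50, 70 and 90.

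**The case against.** The strongest reply is that this is a loose label and the dose itself is settled. There is one formula, it has one free input, and Table 1 supplies that input under columns headed as intensity. Equation 2 follows directly as the term equation 1 needs, and Sections 2.4.7 and 2.4.8 record heart rate lying down, so a resting value is obtainable. Staff could apply equation 2, then equation 1, with the Table 1 percentage, and reach a single answer. This is the likelier reading. It does not remove the problem, because the article never says so, and on that reading Table 1 still misstates the prescribed dose.

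A second reply is that the sentence introducing equation 1 presents the calculation as a safety precaution, so the equation might be a check beside the monitoring. The text does not support a ceiling. The output is named a target, the music is adjusted to reach a target of that name, and no upper limit is mentioned.

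Two further points stand. The bpm figures rest on an assumed resting heart rate; only the expression rest × (1 − p) comes from the document alone. And no safety breach is shown: the article states no intensity limit that the equation 1 targets would exceed, medical staff must approve participation (Section 2.2), and adverse effects and heart rate are recorded (Section 2.3).

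**Conclusion.** The concern holds. The stated and calculated intensities conflict by resting HR × (1 − p), and the gap exceeds the width of a band at every p for resting heart rates of 50–90 at age 72. If equation 1 governs, Table 1 understates the dose throughout and the interval step is little more than half what the table implies.

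The consequence is bounded. Either definition, applied consistently, keeps moderate below high and shifts the shared moderate bands alike in all three programmes. The sample size and tests in Section 2.6 are not affected, and nothing here shows a group comparison to be invalid. It should be fixed because it concerns the intervention's dose in an older population and costs almost nothing to correct.

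**What to change.** Choose one definition and use it in both places.

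- If equation 1 is intended, relabel every aerobic band in Table 1 as percent heart-rate reserve, and confirm clinically that the resulting targets suit participants aged 65 or older.
- If Table 1 is intended, replace equation 1 with target HR = p × maximum HR.

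In either case, report achieved heart rate against the chosen definition.

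The cost is one correction to the table labels or the equation, plus one clinical confirmation if equation 1 is kept. The monitors are already worn in all sessions, so no new measurement is needed.

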## 2. Materials and Methods

### 2.1. Design

This investigation will be based on a randomized intervention, using three different aquatic-based exercise programs conducted in parallel for 28 weeks. The three programs include a continuous aerobic program, an interval aerobic program and a combined (aerobic and muscular strength) program. Variables related to cardiometabolic diseases will be evaluated, i.e., cardiovascular, mental health, and cognitive variables and biochemical markers.

All exercise programs will be conducted at the Piscina Muncipal da Sertã, two times a week (non-consecutive days), with 45-min sessions. All variables related to cardiometabolic diseases will be evaluated at two specific assessment moments: M1, before implementation of the physical exercise programs (baseline) and M2, after the conclusion of the 28 weeks aquatic-based physical exercise programs (post-intervention).

Each evaluation will be divided into three phases: Phase 1—Anthropometry evaluation, physical functions, cognitive and mental health levels; Phase 2—Evaluation of carotid arteries’ intima-media thickness and heart rate variability; and Phase 3—Evaluation of biochemical markers.

The blood collection for biochemical analysis will be conducted by a specialized and certified lab. The measurement of the carotid arteries intima-media thickness will be conducted by a specialist in the area of cardiology. All the remaining data will be collected and organized by the research team members.

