### 2.4. Instruments

#### 2.4.1. Individual Characterization

In the first assessment moment (M1), all participants will fill in a clinical survey to help with the clinical characterization of each participant. This document includes the following information: civil status, regular medication, infections, allergies, diseases, annual doctor consultations, average hours of daily sleep, supplement use, latest blood panel, information on dietary habits, smoking habits and drug use.

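### The age-predicted target heart rate has no stated exception for participants on heart-rate-lowering medication, so a safety calculation can set their effort above its label

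*Protocol article*

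**What the plan says.** Section 2.3 gives one rule for exercise intensity. Equation 1 sets target HR as (maximum HR − resting HR) × intensity + resting HR, and is introduced thus: "As a precaution and safety measure, the intensity will be indirectly calculated using the following equation". Its main input, maximum HR, "is calculated with the following equation for senior populations": Equation 2, 207 − 0.7 × age. No alternative maximum, exception or perceived-exertion check follows.

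Effort is then steered to that target. Sessions are "conducted to the rhythm of music (bpm) that can be adjusted to achieve the target HR", and the section adds: "The intensity of each exercise program will be monitored using the data provided by the Polar V800 and adjusted accordingly".

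Table 1 sets moderate work at 60–65% (weeks 1–13) and 65–70% (weeks 14–28), and high-intensity work at 70–75% and 75–80%. The continuous programme has 30 minutes of moderate work. The interval programme has two 10-minute moderate and two 5-minute high blocks. The combined programme has 15 minutes of moderate aerobic work.

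Section 2.2 admits people aged 65 or over. If they have a comorbidity, "it must be stable and enable participation in aquatic-based exercises classes as approved by local medical staff". Section 2.4.1 has every participant complete a clinical survey at M1 that covers "civil status, regular medication, infections, allergies, diseases, annual doctor consultations", among other items. Section 2.1 places M1 before the programmes start.

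**The concern.** A formula based on age alone cannot register a maximum HR that medication has lowered. For a participant in that position the printed target is a larger share of true capacity than the plan intends, and a calculation offered as a precaution errs upward. Table 1 leaves only 5 percentage points between the top of the moderate zone and the floor of the high zone, so a modest shortfall in true maximum is enough to take moderate work into what the plan calls high.

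The stated safeguards do not change the target. Medical approval decides entry. HR monitoring steers towards the same number. On symptoms, Section 2.3 says "Parameters such as muscle pain, excessive fatigue and general pain will also be reported and inserted in a database", but no rule links those records to the prescription. The medication and disease fields are available before session 1, yet Section 2.3 does not use them.

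**Working it through.** The plan gives no worked target HR, so there is no figure of its own to reproduce. The check is how far true maximum HR must lie below prediction for the moderate zone to reach the planned high-zone floor.

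**Inputs from the document.** Mean age 72.32 (Section 2.2); Equations 1 and 2 (Section 2.3); zones from Table 1.

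**Assumptions.** Resting HR is not given: 60 bpm is used, with 50 to 70 as the range. The drop in true maximum is also not given, so it is solved for.

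**Two readings.** Equation 1 works on HR reserve, whereas Table 1 labels its zones as percentages of maximum HR. Both are computed.

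**Predicted maximum.** 207 − 0.7 × 72.32 = 156.376, or 156.4 bpm.

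**Break-even drop d**, for moderate percentage p and high-zone floor f:
- Equation 1: d = (156.376 − resting HR) × (1 − p/f)
- Table 1 read literally: d = 156.376 × (1 − p/f)

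For example, in weeks 1–13 with resting HR 60, the top of the zone gives 96.376 × (1 − 0.65/0.70) = 6.9 bpm. On the Table 1 reading it is 156.376 × (1 − 0.65/0.70) = 11.2 bpm.

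| Reading | Weeks | Top of moderate zone reaches high floor (bpm) | Whole moderate zone reaches it (bpm) |
|---|---|---|---|
| Equation 1, resting HR 60 (range 50–70) | 1–13 | 6.9 (6.2–7.6) | 13.8 (12.3–15.2) |
| Equation 1, resting HR 60 (range 50–70) | 14–28 | 6.4 (5.8–7.1) | 12.9 (11.5–14.2) |
| Table 1, % of maximum HR | 1–13 | 11.2 | 22.3 |
| Table 1, % of maximum HR | 14–28 | 10.4 | 20.9 |

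At ages 65 and 80 the top-of-zone thresholds are similar: 5.4 to 8.0 bpm by Equation 1 and 10.1 to 11.5 bpm by Table 1.

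**Smaller drops.** At the mean age a 5 bpm drop does not reach the floor on either reading. On the Table 1 reading a 10 bpm drop stops just short: 64.1–69.4% against a 70% floor, and 69.4–74.8% against 75%.

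**What happens to the other zones.** By Equation 1 with resting HR 60 and a 10 bpm drop, every percentage is multiplied by 96.376/86.376 = 1.116:
- Weeks 1–13: moderate 66.9–72.5%, high 78.1–83.7% of true reserve.
- Weeks 14–28: moderate 72.5–78.1%, high 83.7–89.3%.

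The gap between zones becomes 5 × 1.116 = 5.6 points, against the planned 5. All zones move up together.

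**The case against.** **The contrast between programmes.** A reader might infer that the error narrows the difference between continuous and interval training for the participant concerned. The arithmetic does not support this. The high zone moves up with the moderate zone, the gap widens slightly in relative terms, and in bpm it is unchanged. The planned high-zone floor is therefore only a yardstick for how far moderate work has drifted from its label. It does not show that the two kinds of block converge.

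**A condensed article.** The full protocol may contain an exception, and a reader should not infer that none exists. But the article prints both equations, their protective purpose and the zones without qualification. The point concerns what that rule does when followed as printed.

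**Premises not in the document.** No section mentions heart-rate-lowering drugs, how many participants take them or what they do to maximum HR. That such people may be enrolled is inferred from the admission of stable comorbidities. This stands, and it limits the point to a threshold rather than a demonstrated effect.

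**Resting HR.** Equation 1 uses resting HR, which medication may also lower. A fall from 70 to 50 bpm would cut the 65% target by 0.35 × 20 = 7 bpm. This is true, but the break-even formula already uses the participant's own resting HR: at 50 bpm the threshold in weeks 1–13 is still only 7.6 bpm.

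**Safeguards.** Medical approval is specific to aquatic classes, and Section 2.3 says the programmes follow published exercise recommendations. Both soften the concern. Neither is stated to give these participants a different target.

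**Conclusion.** The point holds as a cheap improvement. The printed rule sets too high a relative intensity for any exercising participant whose true maximum HR is below the age prediction, and no exception is stated for those on heart-rate-lowering medication. At the mean age, moderate work starts to overlap the planned high range at a drop of about 6 to 8 bpm by Equation 1, assuming resting HR of 50 to 70, or 10 to 11 bpm on the literal Table 1 reading. The exposure can be up to 30 minutes per session in the continuous programme, whereas Table 1 plans 10 minutes of high-intensity work per session in the interval programme. In that programme, the high blocks of an affected participant also rise above their label.

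A reader might infer that participants will be exercised unsafely. The document does not show that: the high zone is itself prescribed in the interval programme, and both the share affected and the size of any drop are unknown. The supported conclusion is mis-set intensity and a safety calculation that errs upward.

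**What to change.** Before session 1, use the medication and disease fields from the M1 survey to flag exercise participants on heart-rate-lowering medication. After Equation 2, state that the age-based target does not apply to them. Have the medical staff who already approve entry confirm an upper HR limit for each, and guide their moderate and high blocks by perceived exertion, with a separate range for each.

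The cost is two or three sentences in Section 2.3, a check of a form already completed and a short briefing for the exercise technicians. The downside is less precise intensity control for flagged participants, which may slightly blur the contrast between programmes. How much depends on the share flagged, which is not known.
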